### Study treatment

All participants will have started their acute first-line therapy prior to randomization. Participants meeting the definition of incomplete responder may continue to maintain stable doses of background IST throughout the course of the study. To help reduce variability and to facilitate study interpretability, permitted background ISTs are limited to one of either mycophenolate mofetil, intravenous cyclophosphamide, or azathioprine. For incomplete responders who have previously received rituximab, a treatment course must have been initiated ≥2 months prior to screening and the last dose of rituximab must have been administered ≥4 weeks prior to randomization.

After acute first-line therapy, many experts recommend treatment with glucocorticoids, typically at a dose of >20 mg/day. Long-term glucocorticoid use for disease control (usually 3–12 months) is common in AIE, particularly LGI1-IgG+ AIE, and is associated with toxicity, adverse events (AEs), and health risks (28, 101–103). Therefore, participants who receive oral or intravenous glucocorticoids at study baseline are required to taper off using a standard taper schedule, starting 4 weeks after randomization (Week 4), unless they are in a critical-care setting. Because patients with AIE may relapse when reducing their glucocorticoid dose (28, 101), the ability to successfully taper glucocorticoids will be an important outcome of this study.

#### Study treatment: Part 1

During Part 1, participants will receive placebo or satralizumab via subcutaneous (SC) injection at Weeks 0, 2, 4, and then every 4 weeks (Q4W) until the end of Part 1. Part 1 consists of a double-blinded treatment period of 52 weeks, with primary and secondary endpoint evaluation at Week 24. The 24 weeks after initiation of satralizumab represent the period after the acute symptomatic first stage, where recovery would be expected to occur, and long-term prognosis would become evident for newly diagnosed patients. Early response to treatment is correlated with overall clinical improvement and long-term functional outcome improvements in NMDAR-IgG+ and LGI1-IgG+ AIE (46, 55). A 24-week period is expected to capture early response to treatment in both the new onset and the incomplete responder populations and determine the need for any additional lines of therapy. However, some deficits, such as cognitive impairment, may persist for more than a year (44, 104). Therefore, a 52-week double-blinded treatment period was selected to characterize the efficacy of satralizumab on longer-term outcomes of cognition, quality of life measures, and regaining of daily functioning.

A common concern reported in AIE trials is the possibility of being randomly assigned to placebo (82), particularly if participants are required to discontinue all prescribed medications. Considering that AIE can have an aggressive course, all participants are permitted to receive medications that are commonly used for the symptomatic management of AIE, as described by Abboud et al. (28). Dose decreases of symptomatic treatments will only be permitted for safety reasons during the first 24 weeks of Part 1. Additionally, participants classified as incomplete responders are permitted to continue receiving the aforementioned ISTs. Rescue therapy with commonly used medications may be administered to participants who do not improve or worsen during the course of the study, in line with current clinical management practice. Introduction of a new IST, dose increases, change of background treatment, or inability to taper off glucocorticoids due to failure to improve or worsening of disease will be treated as a rescue medication event. The increase in glucocorticoid dose or failure to taper off glucocorticoids according to the protocol-directed taper will be regarded as rescue unless prespecified criteria are met.

#### Study treatment: Part 2

After completing Part 1 of the study, participants can enter Part 2. The long-term consequences of AIE are thought to be critically influenced by treatment in the acute phase and subsequent months (21, 25, 55, 105). However, the benefit of immunomodulation after acute therapy and the optimal duration of treatment are poorly understood. Hence, Part 2 is key to the provision of longer-term data on the risks and benefits of satralizumab in AIE, as well as the generation of robust data on longer-term outcomes and treatment in AIE.

As a requirement to commit to an extension period at enrollment may negatively influence recruitment and retention of participants, an innovative approach is used for Part 2 that is designed to assist in retaining as many participants as possible in a longer-term assessment. Participants can choose a long-term treatment plan that is most suited to their individual clinical response and circumstance. Participants may choose to (1) continue on randomized treatment, (2) initiate open-label satralizumab (participants will continue to receive satralizumab SC Q4W if they were randomly assigned to satralizumab in Part 1 or receive satralizumab per the dosing regimen in Part 1 if they were randomly assigned to placebo), or (3) stop study treatment and continue with follow-up assessments.

Participants may be tapered off any remaining steroids or ISTs at the discretion of the investigator. This is allowed only after Week 12 of the extension period for participants choosing option 2 to ensure that participants treated with placebo in Part 1 have reached steady-state levels of satralizumab prior to glucocorticoid/IST taper. Satralizumab can be self-administered by participants (or their caregivers) who choose option 1 (from Week 0 of the extension period) and option 2 (from Week 24 of the extension period) on days that do not require additional assessments at the site, if deemed appropriate by the investigator. A telephone interview after each satralizumab dose will confirm treatment adherence and evaluate any changes in health status (e.g., new or worsening neurological symptoms or any possible AEs). The option to stop all study treatment is open to all participants at any time during Part 2. In addition, the option to start open-label satralizumab (option 2) is available to participants who chose to continue their original treatment plan (option 1) at any time.

Part 2 was designed to reflect the real-world choices made after receiving acute therapy for AIE. Incorporating patient preference will hopefully maximize the likelihood of patient participation in the extension period and provide insights into long-term outcomes in AIE.

#### Study assessments and endpoints

The choice of appropriate study endpoints has been a significant challenge in AIE trial development (82). For a Phase 3 study, it is important to determine clinically relevant endpoints that have clinical validity and are also sensitive enough to measure the benefit-to-risk profile of an investigational treatment. For AIE, endpoint categories include general measures of disability/functional status, cognitive assessments, and autoimmune encephalitis-focused categorical rating scales. CIELO was designed to use the mRS, a measure that covers the broad range of symptoms that are applicable in both NMDAR-IgG+ and LGI1-IgG+ AIE.

Some previous studies have used the Clinical Assessment Scale in Autoimmune Encephalitis (CASE) scores, clinical worsening (patient or clinician observations, Lawton and Brody Instrumental Activities of Daily Living Scale [IADL]), Texas Functional Living Scale (TFLS), hospitalization (for symptoms of encephalitis), or seizure count measures as the primary endpoint (Table 1) (29, 82, 85, 88, 89); however, these are associated with some limitations. Despite widespread use in AIE clinical trials, CASE has fewer data supporting its applicability for longer-term follow-up and subtler sequelae (53, 106). CASE does not incorporate categories for death, sleep dysfunction, or autonomic dysfunction (13), and there are limited data for its use in pediatric populations (107). As for seizure count, due to inadequate measures of acute seizure reporting available and the fact that not all patients experience seizures, larger sample sizes would be required to demonstrate a clinical effect when measuring clinical worsening or seizure counts as a primary endpoint.

CIELO will use the mRS as the primary outcome measure of both the NMDAR-IgG+ and LGI1-IgG+ AIE basket study arms to evaluate the benefit of satralizumab on clinical status and disability. mRS measures overall disability and has been used in AIE studies for patients with both NMDAR-IgG+ and LGI1-IgG+ subtypes with proven validity and reliability (21, 84, 87, 108, 109) (Table 1). Historically, the mRS has also been used as an outcome measure for infectious encephalitis (110), including as a primary outcome measure in herpes simplex encephalitis studies (111). Available data on the mRS in AIE have been used to help inform the CIELO study design, particularly regarding expected changes in the placebo arm.

As an endpoint that measures disability and patients’ ability to carry out activities of daily living, the mRS may help provide a more comprehensive assessment of therapeutic efficacy than seizure counts or cognitive scoring in patients with NMDAR-IgG+ or LGI1-IgG+ AIE. To enhance the reproducibility and robustness of data, a Structured Interview for the mRS (mRS-SI), adapted from Wilson and Hareendran (112), will supplement the mRS, and the mRS-SI will be tailored to evaluate specific aspects of disability and dependence associated with AIE. A selection of other clinically meaningful patient-reported outcome (PRO), performance-based outcome (PerfO), and clinician-reported outcome endpoints have also been chosen to assess the treatment benefit of satralizumab in CIELO.

#### Efficacy and safety endpoints, assessments, and analyses

The primary efficacy endpoint in CIELO is the proportion of participants with a ≥ 1-point improvement from study baseline in the mRS score and no use of rescue therapy at Week 24 (Table 4). A 1-point change in mRS score is considered to be clinically meaningful based on the severity range covered by the scale grade (113, 114) and is used in clinical practice and observational studies to demonstrate a meaningful change in activities of daily living. Because eligible participants for this study will be impaired in carrying out activities at study baseline (as measured by mRS score ≥ 2), a ≥ 1-point improvement, rather than an mRS score of 0–2, which has been defined as a good outcome in some previous studies (21, 108), will be considered to be clinically significant and meaningful (113, 114) in all participants with differing levels of symptomatology and degree of disability.

**Table 4 tab4:** Study endpoints.

Part 1 (primary treatment period)	
Primary efficacy endpoint	Proportion of participants with mRS score improvement ≥1 from study baseline and no use of rescue therapy at Week 24
Secondary efficacy endpoints^a^	Time to mRS score improvement ≥1 from study baseline without use of rescue therapy Time to rescue therapy Proportion of participants with sustained seizure cessation^b^ at Week 24, and no use of rescue therapy Change in CASE score from study baseline at Week 24 MoCA total score at Week 24 RAVLT score at Week 24 (LGI1-IgG+ AIE cohort) mRS score at Week 24 (as measured on a 7-point scale; NMDAR-IgG+ AIE cohort)
Safety endpoints	Incidence, seriousness, and severity of AEs Change from study baseline in targeted vital signs, clinical laboratory test results, ECG results, weight, height (<18 years only), and C-SSRS
Exploratory endpoints	Degree of disability, clinical severity, mood, quality of life and functional living, based on ClinRO, PerfO, and PRO scales (mRS, CASE, MoCA, RAVLT, BDI-II, EQ-5D-5L and MFIS scores) (change from study baseline and absolute scores) Additional exploratory biomarker assessments, including longitudinal assessments
Pharmacokinetics and pharmacodynamics	Serum IL-6 and soluble IL-6R Serum and/or CSF concentrations of satralizumab

^a^Not in hierarchical order; will be tailored to the individual cohort.

^b^Seizure cessation defined as cessation of seizures for 4 consecutive weeks.

AE, adverse event; AIE, autoimmune encephalitis; BDI-II, Beck Depression Inventory, second edition; CASE, Clinical Assessment Scale in Autoimmune Encephalitis; ClinRO, clinician-reported outcome; CSF, cerebrospinal fluid; C-SSRS, Columbia-Suicide Severity Rating Scale; ECG, electrocardiogram; EQ-5D-5L, EuroQol 5-Dimension 5-level; IL-6, interleukin-6; IL-6R, interleukin-6 receptor; LGI1-IgG+, leucine-rich glioma-inactivated 1 immunoglobulin G antibody-positive; MFIS, modified Fatigue Impact Scale; MoCA, Montreal Cognitive Assessment; mRS, modified Rankin Scale; NMDAR-IgG+, *N*-methyl-d-aspartic acid receptor immunoglobulin G antibody-positive; PerfO, performance-based outcome; PRO, patient-reported outcome; RAVLT, Rey Auditory Verbal Learning Test.

As AIE can have an aggressive course, rapid symptom resolution is critical in preventing potentially permanent residual long-term morbidity and mortality. The need for rescue or repeated rescue therapy, due to failure to improve or worsening of AIE-related symptoms, is indicative of unsatisfactory outcomes. Therefore, when treated with satralizumab, the lack of need for rescue therapy is a key factor suggesting its treatment benefit. Freedom from rescue therapy use, combined with improvements in disability and dependence on the mRS scale in the primary endpoint, will provide an overall clinically relevant measure of an early and durable response.

Although it was ultimately decided not to incorporate the CASE scale as a primary efficacy endpoint, it is a promising tool for evaluating the severity of AIE. The CASE score is positively associated with the mRS (115) and is more representative of the diverse symptomatology of AIE than the mRS (13). Hence, it will be assessed as a secondary efficacy endpoint (Table 4). Other secondary and exploratory efficacy endpoints will assess long-term neurological PROs and PerfOs using the Montreal Cognitive Assessment (MoCA); Rey Auditory Verbal Learning Test (RAVLT); Beck Depression Inventory, second edition (BDI-II); EuroQoL 5-Dimension 5-Level; and Modified Fatigue Impact Scale (MFIS) scores (Table 4), many of which have been used in studies to assess long-term outcomes in patients with AIE (7, 116–118). Due to the global nature of the study, PRO instruments have been translated into local languages to facilitate their use. Additionally, seizure type, frequency, duration, and severity will be captured using a patient/caregiver completed seizure diary, and electroencephalogram assessments will be conducted at select time points in Part 1 of the study. Together, these assessments will provide a global understanding of disease severity and response to treatment.

Safety endpoints on incidence, seriousness, and severity of AEs, as well as change from study baseline in targeted vital signs and laboratory tests, will be assessed (Table 4). To characterize the efficacy of satralizumab treatment on longer-term outcomes, exploratory efficacy endpoints will evaluate the durability of response to satralizumab, time course of efficacy, and time to disease improvement (Table 4).

Efficacy and safety measures will be collected throughout Part 1 and Part 2 at prespecified timepoints. Further subgroup analyses will be performed for participants with probable NMDAR-IgG+ AIE and for adolescent participants.

#### Laboratory and biomarker analyses

To explore the PK, PD, and immunogenicity of satralizumab, serum, plasma, blood, and CSF samples, as appropriate, will be taken prior to each study drug administration at prespecified time points. PK sampling will be used to analyze the impact of a range of covariates on exposure (e.g., sex, race, age, and body weight), and the relationships between exposure and PD, efficacy, immunogenicity, and safety endpoints to support the recommended dose of satralizumab in the NMDAR-IgG+/LGI1-IgG+ AIE population. PD sampling will assess target engagement in response to satralizumab. Immunogenicity sampling will assess antidrug antibodies.

Biomarker analyses will explore whether satralizumab is binding to its intended target (IL-6R) and will help to elucidate the mechanism of action of any underlying treatment effect and disease pathophysiology. These analyses may help to identify biomarkers that are predictive of a response to satralizumab, prognostic biomarkers that are associated with progression to a more severe disease state, and biomarkers associated with susceptibility to developing AEs (that could potentially lead to improved AE monitoring). Exploratory biomarker research may include analysis of NMDAR-IgG and LGI1-IgG, markers of inflammation, immune cell subset activity, CNS damage, and blood samples for flow cytometry of immune cell subsets and T-, B-, and natural killer cells. CSF sampling is included as an optional study activity at prespecified timepoints in Part 1. While lumbar puncture is routine in the diagnostic workup of AIE, research-based lumbar punctures may not be feasible for all patients and may add a potential barrier to recruitment and retention. Therefore, study lumbar punctures have been made optional.

#### Statistics

The CIELO study will compare satralizumab with placebo in approximately 152 participants with NMDAR-IgG+ or LGI1-IgG+ AIE, as defined by the study eligibility criteria. The NMDAR-IgG+ and LGI1-IgG+ AIE cohorts will be treated as separate populations and analyzed separately. Each cohort will have independent Type I error control at a two-sided 5% significance level. For adolescent participants, descriptive subgroup analyses will be performed and compared with data collected in adults to check for consistency in any observed treatment effect, and that adolescent data are comparable to the data obtained from the overall population.

Efficacy and safety analyses will be performed in the intent-to-treat and safety populations, respectively. The primary comparison of interest in each cohort is the difference between the placebo and satralizumab groups in the proportion of participants who achieve the primary endpoint, which will be tested using a Cochran–Mantel–Haenszel test by randomization stratification factors (patient population: new onset versus incomplete responders, and region: North America/Europe versus Asia versus rest of world).

Secondary efficacy endpoints will follow a cohort-specific hierarchy, allowing analyses to be tailored to the predominant clinical features and longer-term impairments in the NMDAR-IgG+ and LGI1-IgG+ AIE populations. An independent data monitoring committee will be used for data review during Part 1.

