#### Study-wide eligibility criteria

Eligible participants must meet the definition of new onset or incomplete responder AIE, as defined in Table 2. The study aims to recruit both populations in representative proportions. Other key inclusion criteria include: (1) the onset of AIE symptoms ≤9 months before randomization, to ensure that patients who have an active state of inflammatory disease are enrolled, as opposed to patients who may have temporal atrophy, encephalomalacia, and long-term sequelae as a consequence of previous AIE episodes, and (2) a stable (≥24 h) mRS score of ≥2 at study baseline (Part 1, Week 0, pre-dose assessments). Patients with mRS scores of ≥2 will be included to ensure representation from patients whose deficits, such as cognitive deficits, persist despite prior treatment and “mild” mRS scores.

After providing informed consent, participants will enter a screening period of up to 28 days. For participants otherwise unable to give consent due to the severity of their disease, informed consent may be given by a legally authorized representative (or equivalent under local law) and participant assent obtained, as per local requirements.

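### The stated primary test leaves out baseline mRS, the reference value of the responder endpoint; the test is valid but can forgo precision in two small, separately analysed cohorts

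*Protocol article*

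**What the plan says.** The Statistics section of the protocol article names the primary comparison in each cohort as a difference in responder proportions, "which will be tested using a Cochran–Mantel–Haenszel test by randomization stratification factors (patient population: new onset versus incomplete responders". The same sentence adds region in three levels and no further factor, so the test has 2 × 3 = 6 strata.

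Table 4 defines the endpoint as "Proportion of participants with mRS score improvement ≥1 from study baseline and no use of rescue therapy at Week 24". Under Study-wide eligibility criteria, entry requires "a stable (≥24 h) mRS score of ≥2 at study baseline", assessed before the first dose. Baseline mRS is therefore available for every randomised participant. The endpoint section defends the 1-point rule as meaningful "in all participants with differing levels of symptomatology and degree of disability", so a spread of baseline severity is expected.

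On size, the Statistics section gives only a total: "The CIELO study will compare satralizumab with placebo in approximately 152 participants with NMDAR-IgG+ or LGI1-IgG+ AIE". It adds: "The NMDAR-IgG+ and LGI1-IgG+ AIE cohorts will be treated as separate populations and analyzed separately". On error control: "Each cohort will have independent Type I error control at a two-sided 5% significance level".

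**The concern.** The endpoint is a change from baseline, so the same Week 24 state can count differently according to where a participant started. Someone who enters at mRS 5 and settles at 3 meets the mRS component; someone who enters at 2 and stays at 2 does not. Baseline mRS is thus a natural candidate predictor of response, it is already collected, and the stated test does not use it.

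Two things are at stake. If baseline mRS predicts response in either direction, variation that could be explained stays in the error term and power is forgone. And in cohorts of this size the arms will often differ by chance in baseline mRS. Nothing in the stated stratification or primary test adjusts for that, which makes a single observed difference harder to interpret.

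**Working it through.** **No figure to reproduce.** The article states no power, response rates, effect size, allocation ratio or cohort sizes. The section on study assessments says that existing mRS data informed the expected placebo changes, but gives no rate.

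**Inputs.** From the article: about 152 participants in total, two cohorts analysed separately, two-sided 5% in each, 6 strata. Assumed: 152/2 = 76 per cohort (range 60 to 92), 1:1 allocation (38 per arm), placebo response 40%.

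**1. How scarce is precision?** For n per arm, solve for the difference d = p₂ − p₁ that gives 80% power:

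n = [1.96·√(2p̄(1−p̄)) + 0.842·√(p₁(1−p₁) + p₂(1−p₂))]² / d²

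With n = 38 and p₁ = 0.40, d = 0.314. Check: (1.377 + 0.561)² / 0.314² ≈ 38. For placebo rates of 30 to 50%, d is about 30 to 32 points at N = 76, 33 to 35 at N = 60 and 28 to 29 at N = 92.

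**2. Chance imbalance.** If half the participants have high baseline mRS, the between-arm difference in that share has SD = √(2 × 0.5 × 0.5 / 38) = 0.115.

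| N per cohort | SD | P(gap ≥10 points) | P(gap ≥20 points) |
|---|---|---|---|
| 60 | 0.129 | 44% | 12% |
| 76 | 0.115 | 38% | 8% |
| 92 | 0.104 | 34% | 6% |

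The effect on the unadjusted difference is the imbalance times the gap in response between high and low baseline mRS. For illustrative gaps of 20 and 40 points, one SD moves it by 11.5 × 0.20 = 2.3 and 11.5 × 0.40 = 4.6 points.

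**3. Power forgone.** Simulation: 5,000 trials per scenario, N = 76, permuted blocks within the 6 strata, baseline mRS 2/3/4/5 at 25/30/25/20%, marginal response held at 40% versus 71%. The slope is the change in log-odds of response per mRS grade; 0.3, 0.6 and 1.0 are odds ratios of e^0.3 = 1.35, e^0.6 = 1.82 and e^1.0 = 2.72 per grade. The adjusted test is a linear model with population, region and baseline mRS.

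| Slope | Planned CMH | Adjusted linear test | Difference (points) |
|---|---|---|---|
| −1.0 | 79.0% | 86.6% | +7.6 |
| −0.6 | 77.7% | 81.1% | +3.4 |
| 0 | 79.3% | 78.6% | −0.7 |
| 0.3 | 79.0% | 79.2% | +0.2 |
| 0.6 | 79.3% | 81.9% | +2.6 |
| 1.0 | 78.1% | 85.6% | +7.5 |
| 1.5 | 77.6% | 91.5% | +13.9 |

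Simulation error is about 0.6 points. With no treatment effect, the planned CMH rejected in 4.7 to 5.3% of trials and the adjusted test in 4.6 to 5.3%. A separate run at the same size and response rates, with mRS in three levels, gave about 0 to −1 point at slopes 0 to 0.3, about 1 to 2 at ±0.6 and about 7 at 1.0, with null rejection of about 4 to 5%.

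**4. Which adjustment?** At N = 76:

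- Adding all four mRS grades to the strata makes up to 6 × 4 = 24 cells, about 76/24 ≈ 3 participants each. Power is 66.5% at slope 0, 70.7% at 0.6 and 75.1% at 1.0, below the planned CMH each time. It overtakes only at 1.5 (82.9%).
- A CMH by population and three mRS levels drops region. With a weakly prognostic baseline (placebo response 35 to 65% across grades) it had 75.3% power against 76.0% for the planned test.
- A logistic score test with baseline mRS gained power, but its null rejection was about 5.3 to 6.1%. A plain logistic likelihood-ratio test ran at 6 to 7%.

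**The case against.** A CMH test by the randomisation factors is a standard and valid primary test. A reader might infer that chance imbalance biases it or inflates its error rate. It does not: such imbalance is already covered by the 5% level, as the null simulations show. This objection stands in full, and the cost is precision and interpretability only.

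A reader might also infer that baseline mRS is the strongest predictor of response, so that each cohort certainly loses power. The article does not support this. Rescue use counts as failure, and more severe participants may have more room to improve but also more need of rescue, so the net slope could be near zero. New onset versus incomplete responder is a rival predictor and is already in the test. This also stands: the loss depends on a slope that no document gives. It vanishes, however, only if the opposing effects nearly cancel, since a negative slope costs as much as a positive one.

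Finally, because Table 4 lists MoCA, RAVLT and the 7-point mRS as Week 24 scores, one might infer that they will be analysed without their baselines. Table 4 names variables, not models. Those models belong to the analysis plan, which is not shown, so nothing can be concluded. That plan may also hold a supporting analysis with baseline mRS; the point here is limited to the primary test as stated.

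**Conclusion.** The point holds as one of efficiency, not validity. The stated primary test omits a baseline value that every participant has and that defines the endpoint. With marginal response rates fixed, the power forgone is about 0 points at slopes of 0 to 0.3 per grade, about 1 to 3 at 0.6 in either direction and about 7 to 8 at 1.0. The larger loss at 1.5 needs a very steep relation for which the article offers no evidence.

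These sizes rest on assumed values for the cohort split, allocation ratio, response rates, baseline mRS distribution and slope. The structural part rests on the article alone: separate small cohorts, no baseline mRS in stratification or test, and hence no adjustment of the primary comparison if the arms differ on it.

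**What to change.** Before unblinding, prespecify as the primary analysis in each cohort a covariate-adjusted risk difference with population, region and baseline mRS (2, 3, ≥4). Use a linear model with robust variance, or an equivalent standardised estimator. It still targets the difference in proportions. Name the estimator and its variance, and confirm by simulation that type I error holds at the planned cohort sizes; the null rates above cover only the linear tests that were simulated. Keep the planned CMH as a sensitivity analysis.

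Do not add every mRS grade as further CMH strata, and do not replace region by mRS in the CMH.

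The cost is a wording change in the protocol or analysis plan, with no new data and no extra participants. The downside is at most about 1 power point if baseline mRS proves not to be prognostic.
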